#### Analysis of Secondary Outcomes

##### Perceived Usability and App Engagement

Based on the results of the feasibility study and the nature of the behavior regulation strategies, we expect an engagement pattern in frequency, type, and depth of engagement that differs for each behavior change strategy and changes over time. Specifically, for Insight Cards, we believe that patients will actively engage with this component during treatment (ie, creating Insight Cards during use), but shift to more passive engagement (ie, reading the input, but only creating new content at limited occasions) during follow up. For Value-Based Goals, we expect that the formulation of goals and steps will increase during the final part of treatment, together with a growing emphasis within the treatment program on integrating newly learned strategies into daily life routines. After treatment, we anticipate that patients will engage in a reflective (eg, documenting progress) and active (ie, formulating new goals) manner with this strategy. In general, we expect a decreasing trend of the number of logins over time, but an increase in the “depth” of use (ie, the average number of features accessed per login) as well as an increase in the duration of a login. We will calculate descriptive statistics to explore patterns of engagement. Furthermore, to examine the extent to which user engagement and usability are negatively associated with the change of pain disability during follow up, we will perform a multiple regression analysis, with the change score of pain disability (t_4_ – t_1_) as the outcome variable and engagement and usability measures as predictors. We will adjust for age, sex, pain intensity, and baseline PDI.

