### Mobile Health

The emergence of mobile health (mHealth) provides new opportunities to support behavior regulation to maintain or enhance the long-term treatment effect of IMPT programs. Despite substantial variations concerning study quality, interventions, and outcomes, mHealth apps are generally regarded as a promising strategy to facilitate adherence to treatment principles or to increase self-management skills (eg, [25,26]). A specific advantage is that an app can include multiple interacting behavior regulation strategies within its digital environment (eg, automatically linking personalized goal setting regarding physical activity to accelerometer output). Moreover, mHealth strategies can integrate other smartphone functionalities such as digital calendars, instant messaging services, or a camera, thereby offering personalized behavior regulation strategies that support the transfer of treatment insights into each patient’s personal environment.

Despite the potential and current popularity of mHealth apps, the effectiveness on health-related outcome measures varies greatly [27]. Factors such as engagement—defined as the extent of app use as well as the corresponding subjective experience [28]—and usability—defined as the relative ease with which users can use an app to achieve a particular goal [29,30]—may account for this variability [27,30]. For example, patients that use an app to change their health behaviors may use the app in a different way than intended or stop using the app after several days, which prevents facilitating the intended behavior change [28]. Therefore, evaluations concerning the effectiveness and clinical importance of mHealth apps on health outcomes should take evaluations on user engagement and perceived usability into account [30,31].

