**Engagement and usability**				
	Overall engagement	The level of engagement and usability will be positively associated with a change in pain disability during follow up (*t*_4_^l^ – *t*_1_).	1. System usability scale^f^ 2. System usage data of AGRIPPA app (see below)	Multiple linear regression
	Frequency of engagement	How does the frequency of engagement vary over time after treatment?	Average number of logins per week	Descriptive statistics
	Depth of engagement	How does the average number of features accessed per login vary after treatment?	Average number of features accessed per log-in	Descriptive statistics
	Duration of engagement	How do the average minutes spent at each login as well as the total time spent with the app per week vary after treatment?	1. Average minutes spent at each login. 2. Total time spent with the app	Descriptive statistics
	Active engagement with Insight Cards	To what extent will the number of created Insight Cards increase or decrease after treatment?	Number of Insight Cards created	Descriptive statistics
	Active engagement with VBG^m^	To what extent will the number of created VBG cards increase or decrease after treatment?	1. Number of VBGs created. 2. Number of steps created	Descriptive statistics

^a^IMPT: interdisciplinary multimodal pain therapy.

^b^PDI: Pain Disability Index.

^c^Outcome measure is part of routine care.

^d^GPE: global perceived effect.

^e^*t_1_*: immediately postintervention.

^f^Outcome measures will be obtained with an additional electronic survey.

^g^SF-12: 12-item short-form health survey.

^h^iPCQ: iMTA Productivity Cost Questionnaire.

^i^IPQ-K DLV: Dutch language version of the Illness Perception Questionnaire.

^j^PSEQ: Pain Self-Efficacy Questionnaire.

^k^NRS: numeric rating scale.

^l^*t_4_*: 12 months postintervention.

^m^VBG: Value-Based Goals.

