##### System Usage Data

To obtain insight into the frequency, intensity, and duration of engagement, we will obtain the following system usage data for each time point: average number of logins per week, average number of features accessed per login, average minutes spent with the app at each login, total time spent with the app per week, number of Insight Cards created, number of value-based goals created, and number of steps created within the Value-Based Goals module**.**

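### Depth and login duration are per-login averages with no value for patients who have stopped, so selective stopping alone can produce the predicted rise

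*Protocol article*

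**What the plan says.** Table 1 (Engagement and usability) defines depth of engagement by one measure, the "average number of features accessed per login", and asks: "How does the average number of features accessed per login vary after treatment". For duration it asks: "How do the average minutes spent at each login as well as the total time spent with the app per week vary after treatment". The System Usage Data section lists, for each time point, "average number of features accessed per login, average minutes spent with the app at each login, total time spent with the app per week", together with logins per week and counts of Insight Cards, value-based goals and steps created.

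The section Perceived Usability and App Engagement states the expected pattern. It begins "In general, we expect a decreasing trend of the number of logins over time" and continues with a predicted increase in depth, "ie, the average number of features accessed per login) as well as an increase in the duration of a login". The patterns will be examined with descriptive statistics. The same section plans a regression of the change in pain disability from the end of treatment to 12 months on engagement and usability measures, without naming which of the seven usage measures enter.

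Three other places bear on this. The Mobile Health section notes that app users may "stop using the app after several days, which prevents facilitating the intended behavior change". The Participant Timeline leaves use after treatment to the patient. Strengths and Limitations says that comparing usage data with the stated expectations will give some indication of adherence.

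**The concern.** A per-login average is a ratio with logins in the denominator. For a patient who did not open the app in an interval it is 0/0. Such a patient adds nothing to the interval's average, whether that average is a mean of patient means or is pooled over logins. The average at 12 months may therefore describe a smaller and different group from the average at the end of treatment.

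The article forecasts fewer logins and deeper, longer logins together. Loss of lighter users produces that same combination with no change in any individual. Because agreement with the forecast is to be read as a sign of adherence, a pattern that abandonment can create could be counted as evidence of sustained use. Engagement is one of the three main objectives, although an exploratory one.

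The regression has a related exposure. If per-login measures over a period are used as predictors, patients with no logins in that period have no predictor value. They are the patients at the low end of the association that hypothesis 3 asks about.

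**Working it through.** The article gives no usage figures, so there is none to reproduce. All usage values below are assumptions chosen to show the mechanism.

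**Number of app patients.** The Abstract plans 158 patients and the Design section allocates 1:1, so 158 / 2 = 79.

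**Arithmetic illustration.** Assume 40 light users (2 features and 3 minutes per login) and 39 heavy users (5 features and 8 minutes per login). No patient's per-login use ever changes.

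- Start, features per login: (40 × 2 + 39 × 5) / 79 = 275 / 79 = 3.48.
- Start, minutes per login: (40 × 3 + 39 × 8) / 79 = 432 / 79 = 5.47.

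Let a share of the light users stop, leaving *r*. The averages among those still logging in are (2*r* + 195) / (*r* + 39) and (3*r* + 312) / (*r* + 39).

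| Light users who stop | *r* | Features per login | Minutes per login |
|---|---|---|---|
| 0% | 40 | 3.48 | 5.47 |
| 25% | 30 | 3.70 | 5.83 |
| 50% | 20 | 3.98 | 6.31 |
| 75% | 10 | 4.39 | 6.98 |
| 90% | 4 | 4.72 | 7.53 |

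The within-patient change among continuing users is exactly 0 in every row.

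**The same 50% row on totals.** Assume also that each active user logs in once a week. Over all 79 patients, with zeros for the 20 who stopped:

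- features per week fall from 275 / 79 = 3.48 to 235 / 79 = 2.97;
- minutes per week fall from 432 / 79 = 5.47 to 372 / 79 = 4.71;
- logins per week fall from 1 to 59 / 79 = 0.75.

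Totals per week and depth per login are different quantities. The comparison shows only that they move in opposite directions here. A mean of 0.75 logins per week would also arise if all 79 patients carried on at 0.75 logins a week, so that average alone does not show that anyone stopped.

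**Dependence on who stops.** A simulation (2000 replicates) used 79 patients with fixed lognormal depth (median 3, log SD 0.4). About half were still using the app, with log-odds of continuing equal to *b* × standardised log depth.

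| *b* | Mean depth, all patients | Mean depth, still using | Mean apparent change | Replicates showing a rise |
|---|---|---|---|---|
| −0.5 (deeper users stop more) | 3.25 | 2.95 | −9% | 2% |
| 0 (unrelated) | 3.25 | 3.25 | 0% | 50% |
| 0.5 (lighter users stop more) | 3.25 | 3.56 | +9% | 98% |
| 1.0 (lighter users stop more) | 3.25 | 3.79 | +17% | 100% |

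The artefact therefore needs lighter users to stop more often.

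**The case against.** Five of the seven listed usage measures are defined at zero use: logins per week, total time per week, Insight Cards, value-based goals and steps created. A reader might infer that an app abandoned by most patients would simply be reported as showing deepening engagement. The article does not support that. It forecasts falling logins openly, and mass abandonment would be visible in these measures beside the per-login figures. Duration also has a total-time measure that can keep zeros. What remains is that an average of logins or minutes does not separate stopping from lighter use, and that depth has no companion measure defined at zero use.

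A second tempting reading is that the regression would be confined to continuing users. That is not established either. The predictors are not named and no measurement window is given. Hypothesis 3 lists usability, frequency of use, duration of use and reported adherence, but not depth. If use were averaged over the whole period of access, only patients who never logged in would lack a value.

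It can also be said that nothing in the article shows lighter users stopping first, that the Mobile Health remark concerns apps in general, and that a fall in logins may mean less frequent use. All of this is fair, and it is why the claim is limited to what can happen. Finally, handling of zero-use intervals may be set out in a full analysis plan. That would be a good place for it, but the depth measure, the predicted direction and the way agreement will be read are already fixed in the article, and together they cannot tell deepening use from selective loss of users.

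**Conclusion.** The point holds in conditional form. The two quantities predicted to rise are undefined for patients with no logins. If lighter users stop more often, they can rise with no within-patient change, and the article would count that as a sign of adherence. Under the assumed values the apparent rise in depth is about 9% to 17% in the simulation. In the arithmetic example it runs from 6% (3.70 / 3.48) to 36% (4.72 / 3.48). If stopping is unrelated to depth there is no systematic rise, and if deeper users stop more often there is an apparent fall of about 9% at the strength tried. These sizes rest wholly on assumed usage and stopping patterns.

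The consequence is confined to the reading of engagement and adherence, and possibly to the set of patients in the engagement regression. The primary outcome and the cost-effectiveness result are untouched. This is a cheap and worthwhile improvement to an exploratory objective.

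**What to change.** In Table 1 and in Perceived Usability and App Engagement:

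- For each interval, report the proportion of app-arm patients with at least one login.
- Summarise logins, minutes and features per week over all app-arm patients, with zero for those who stopped. Features per week is features per login multiplied by logins per week for each active patient, which gives depth a companion defined at zero use.
- Assess change in per-login depth and duration only within patients who logged in during both intervals compared, and label it as conditional on continued use.
- In the regression, make sure that patients without logins are not dropped. One way is to use measures defined at zero use (logins per week, total time) as the main engagement predictors, with per-login measures as supplementary predictors among users. This keeps depth as a construct; replacing every per-login predictor with a total would not.

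The cost is a few lines of text and minor programming, since the app developer already supplies the usage data. The reported engagement trend may look less favourable.

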### Study Objectives

The present trial has three main objectives. Our first objective is to evaluate the effectiveness of the AGRIPPA intervention (ie, enhanced treatment condition) on pain disability for patients with chronic musculoskeletal pain who participate in an IMPT program compared to a usual care control group with a follow-up period of 12 months. Our second objective is to determine the cost-effectiveness of the AGRIPPA intervention relative to usual care. Our third objective is to explore the level of engagement and perceived usability of patients that use the app. We have formulated three hypotheses: (1) the maintenance of improvement in pain-related disability over time after IMPT will be more favorable for the enhanced treatment condition compared to usual care; (2) the effect of the app on pain disability will translate to less health care utilization and less societal costs (eg, less absenteeism), leading to a cost-effective intervention compared to treatment as usual; and (3) for participants in the enhanced treatment condition, the perceived usability, frequency of use, duration of use, and reported adherence to the AGRIPPA app will be positively associated with a favorable change over time of pain-related disability.

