#### Sample Size Calculation

The sample size calculation is based on a 2-factor repeated-measures analysis of variance with within-factor time (5 levels) and between-factor treatment (2 levels) conditions on the outcome variable PDI. We have set the α to .05, the power (1 – β) to .95, and assumed a moderate treatment effect (*f*=0.2). To account for the expected dependencies of patients within each of the 5 participating treatment locations, we applied the Donner et al [55] formula for the variance inflation factor, assuming an intracorrelation coefficient of 0.2 [56,57]. Furthermore, we corrected the analysis for an expected attrition of 20%, which is based on the average attrition of similar studies that used the PDI [21,58,59]. Based on these calculations, a minimum sample size of 157 participants, equally divided over 5 treatment locations, will be required.

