##### Missing Data

Following recommendations of Twisk and colleagues [69], we will perform the multilevel analysis on incomplete data, rather than using multiple imputation procedures. However, we will use the R MICE package to search for patterns of missing data across the included variables and to perform *t* tests to explore the relationships between the amount of missingness of each variable and all other variables [70].

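### The hypothesis 3 regression on PDI change t4 − t1 cannot score patients who lack either visit and leaves the 3- and 6-month PDI unused; the engagement slope is attenuated if dropout depends on both low use and worsening

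*Protocol article*

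**What the plan says.** Study Objectives states hypothesis 3 for the app arm only: "for participants in the enhanced treatment condition, the perceived usability, frequency of use, duration of use, and reported adherence to the AGRIPPA app" are expected to go with a favorable change in disability.

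The test is fixed in two places. Table 1 names multiple linear regression for the change between t1 and t4. The section on perceived usability and app engagement says "we will perform a multiple regression analysis, with the change score of pain disability", taken as t4 minus t1. The predictors are the measures of engagement and of usability. The covariates are listed next: "We will adjust for age, sex, pain intensity, and baseline PDI". PDI at t2 and t3 appears nowhere in this model, although the Participant Timeline schedules data collection at 3 and 6 months and Table 1 marks PDI as part of routine care.

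The Sample Size Calculation reports that "we corrected the analysis for an expected attrition of 20" percent, without attaching it to a visit or an arm. The Missing Data section says "we will perform the multilevel analysis on incomplete data, rather than using multiple imputation procedures". It adds that "we will use the R MICE package to search for patterns of missing data across the included variables" and to run t tests on missingness. It does not mention the hypothesis 3 regression.

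**The concern.** The primary PDI analysis and the hypothesis 3 analysis share an outcome scale and will share the same dropout, but they treat it differently. The multilevel model uses every visit a patient supplies. The change-score regression needs both t1 and t4, so a patient followed to 6 months and then lost contributes nothing.

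Hypothesis 3 is about patients who use the app little and relapse. The Mobile Health section itself says that users may "stop using the app after several days, which prevents facilitating the intended behavior change". If patients who disengage and worsen are also the ones who stop answering questionnaires, the regression loses the records that carry the association. The slope then moves toward zero, and a weak result would partly reflect who could be scored.

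**Working it through.** **1. The plan's own sample size.** Inputs from the Sample Size Calculation: f = 0.2, 2 groups, 5 time points, α = 0.05, power 0.95, ICC 0.2, 5 locations, 20% attrition. The correlation between repeated measures is not given; 0.5 is assumed.
- Interaction test: λ = f²·N·m/(1 − ρ) = 0.04 × 48 × 5/0.5 = 19.2, with 4 and 184 degrees of freedom, gives power 0.952, so N = 48.
- Variance inflation: 1 + (48/5 − 1) × 0.2 = 2.72; 48 × 2.72 = 130.56.
- Attrition: 130.56 × 1.2 = 156.67, rounded up to 157. This matches the stated minimum.

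**2. Patients without a change score.** Planned recruitment is 158 at 1:1, so 158/2 = 79 in the app arm. If 20% lack t4 in that arm, 79 × 0.20 = 15.8 (about 16) are unscored and about 63 remain.

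**3. Precision.** For one engagement measure with four covariates, power = Φ(atanh(r)·√(n − 4 − 3) − 1.96).

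| Assumed partial r | n = 79 | n = 63 |
|---|---|---|
| 0.2 | 0.41 | 0.33 |
| 0.3 | 0.75 | 0.64 |
| 0.4 | 0.95 | 0.89 |

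**4. Bias when worsening is visible by 6 months.** Simulations with 20% missing t4. Slopes are PDI points per SD of engagement; negative means more use, less relapse. All slopes, SDs and dropout strengths are assumptions.

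(a) True slope −2, n = 79, 4,000 runs; random intercept SD 11, random slope SD 6 per year, residual SD 6; no covariates:

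| Dropout depends on | Complete cases | Likelihood using t1–t3 |
|---|---|---|
| nothing (random) | −2.04 | −2.03 |
| worsening by 6 months | −1.90 | −1.99 |
| worsening and low use | −1.41 | −2.02 |

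The last row is an attenuation of (2 − 1.41)/2 = 30%. The sampling SD is 1.32–1.40 for complete cases and 1.29–1.35 for the likelihood analysis, so using t2 and t3 removes bias but regains little precision.

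(b) True slope −2, adjusted for t1 PDI: about −2.0 for random or low-use-only dropout, −1.92 (4%) for worsening only, and −1.78 to −1.49 (11% to 26%) for worsening plus low use. Using t1–t3 gives about −2.0.

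(c) Logistic dropout on standardised t3 worsening and low engagement, adjusted for t1 PDI: −1.82 (9%) at log-odds 0.5 per SD each, and −1.52 (24%) at log-odds 1 each.

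(d) Dropout concentrated in low users with a t3 rise above 8.5 points (the lower end of the plan's clinically important change), at 40%, 60% and 80% in that group. A true slope of −4 gives −3.68, −3.31 and −2.89 (8%, 17%, 28%). A true slope of −2 gives −1.71, −1.38 and −1.03 (15%, 31%, 49%). Using t3 PDI returns −4.01 throughout in the first case, and −2.00, −2.00 and −1.99 in the second.

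**5. Bias when worsening is not seen before dropout.** With dropout driven by t4 worsening plus low use (log-odds 1 each), the likelihood analysis itself gives −1.32 against −2, still 34% attenuated.

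**The case against.** Five points can be made on the other side.

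- **The article does not say that incomplete patients will be dropped.** It declines multiple imputation only for the multilevel analysis, so a full analysis plan could still impute t4 for this regression. This stands: a reader might infer that the plan prescribes complete-case deletion, and it does not. What is fixed is an outcome and model with no place for the t2 and t3 PDI.
- **The analysis is exploratory.** The third objective is to explore, and Strengths and Limitations uses that word for the engagement analysis. This stands and limits the severity, although a directional hypothesis is stated and a test named.
- **Nothing shows that low users stop answering questionnaires.** PDI comes through routine care outside the app, and email and telephone reminders are planned. This also stands: the link is plausible but assumed.
- **The bias is small beside the noise.** In simulation (a) the worst bias, 2.00 − 1.41 = 0.59, is under half the sampling SD of 1.32–1.40. A reader might infer that hypothesis 3 would fail because of dropout; low precision is the larger threat.
- **A bare mixed model is not a full repair.** It could lose the planned covariates, would still drop patients whose usability score is missing (that score comes from the additional survey), and cannot fully correct for unseen late worsening. This stands and shapes the fix.

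**Conclusion.** The point holds in a conditional form. The stated outcome leaves patients without t1 or t4 PDI unscored (about 16 of 79 if the 20% applies to t4 in the app arm) and sets aside PDI already collected at 3 and 6 months. Random or low-use-only dropout costs precision only. Dropout that depends on both low use and worsening attenuates the engagement slope, by roughly 10% to 30% when the worsening shows by 6 months. That range rests on assumed slopes, SDs and dropout strengths; the harshest setting tried reached about half.

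Two stronger readings are not supported. The documents do not show that the slope will be biased, because no passage links dropout to both use and outcome. Nor is 30% an expected bias: in simulation (a) it is the worst of three assumed mechanisms, from a model without the planned covariates.

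The severity is minor to moderate, since the primary analysis and the treatment comparison are not touched.

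**What to change.** In the engagement analysis section and Table 1, replace the change-score regression with a linear mixed model in the enhanced arm:

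- Outcome: PDI at t1, t2, t3 and t4, with categorical time.
- Predictors: engagement-by-time and usability-by-time terms.
- Covariates: age, sex, pain intensity and baseline PDI as now planned, each with its time interaction, so that the reported contrast keeps the same adjustment.
- Report: the engagement effect on the t4 minus t1 contrast.

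State which visit baseline PDI means. Data Analysis labels the pre-treatment visit as baseline, in which case t1 can stay in the outcome. If t1 is meant, make it a covariate, model t2 to t4, and report the engagement effect at t4.

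An equivalent option is to keep the regression and multiply impute t4 PDI and missing usability scores from t1–t3 PDI and the usage data. This does not conflict with the Missing Data section, which declines imputation for the multilevel analysis only. If the mixed model is chosen, say how missing usability scores are handled. In both cases define engagement over a window that does not depend on how long the patient stays in follow-up.

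Add a sensitivity analysis for dropout that depends on unobserved worsening after 6 months, which neither route fully corrects.

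The cost is a change of wording and a little more analysis work. No new PDI data are needed.
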